### Sample size {14}

A total of 600 newborns will be recruited. For the primary outcome, we predict raised AGP (> 1 g/L) in 35% infants at age 6 months in the control group [22]. The study requires a total of 524 infants (131 per am) to demonstrate a 50% reduction (relative risk = 0.50) in the prevalence of the primary outcome from 35% in the control arm to 17.5% in any of the intervention’s arms with 80% power and *α* = 0.0167. The alpha of 0.0167 is required to allow for three comparisons, one for each intervention arm, against the control arm. We will recruit 150 infants per group to allow for 13% dropouts.

We have used AGP concentration as a dichotomous outcome as a conservative approach as we wish to recruit sufficient numbers of children to compare other important biomarkers between groups. Using values of biomarkers as continuous variables will increase the power of the study to detect differences between the study arms. Using AGP as an example, we predict a mean log_10_ value of − 0.24 g/L in controls based on data from Zimbabwe [20]. In total, 102 infants in the intervention and the control group are required to show that mean AGP concentration is 20% lower in the intervention compared with the control group with 90% power at the 5% significance level.

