Analysis of the secondary endpoints with single measurements will also be presented in the ITT and per-protocol (PP) populations and in a similar fashion as for the primary endpoint analysis using generalised linear method. The PP population will be all randomised study subjects who complete 75% or more of the supervised doses. For continuous outcomes, normal distribution and identity link function will be used, from which mean difference together with its 95%CI will be derived. Generalised linear mixed model (GLMMIX) will be employed for the analysis of secondary outcomes with repeated measurements. The GLMMIX model will have treatment, visit, interaction between treatment and visit as fixed effects, baseline measurement of an outcome as covariate, and subject as random effect. The treatment difference between two treatment arms at each visit together with its 95% confidence interval will be derived from the GLMMIX model. Missing data will be treated as missing completely at random in the GLMMIX model analysis and no imputation of primary or secondary endpoints will be made. For the analysis of binary secondary outcomes with repeated measurements, the GLMMIX model will have a binomial distribution and logit link function. The odds ratio between two treatment arms at each visit together with its 95% confidence interval will be derived from the GLMMIX model. For the analysis of continuous secondary outcomes with repeated measurements, the GLMMIX model will have a normal distribution and identify link function. The mean difference between two treatment arms at each visit together with its 95% confidence interval will be derived from the GLMMIX model.

For anthropometric outcomes, *z* scores will be calculated using the WHO Anthro Survey Analyser and WHO 2006 child growth standards [47]. Analyses will include both the comparison of anthropometric indices between intervention groups at different time points and also growth expressed as change in indices over time.

Analyses of the potential adverse effects of the dietary supplements will be done in the safety population.

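### Continuous biomarkers get a normal, identity-link model with a mean difference and no stated transformation, although continuous AGP was planned on the log10 scale: a small power cost for AGP, possibly a large one for more skewed markers

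*Protocol article*

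**What the plan says.** The section on statistical methods for primary and secondary outcomes {20a} sets one model for all continuous secondary outcomes. For single measurements: "For continuous outcomes, normal distribution and identity link function will be used", giving a mean difference with a 95% confidence interval. For repeated measurements: "For the analysis of continuous secondary outcomes with repeated measurements, the GLMMIX model will have a normal distribution and identify link function", again with a mean difference at each visit. (The link named there is evidently the identity link.) The analysis text mentions no transformation, geometric mean or ratio for continuous outcomes.

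The outcomes covered, listed under Outcomes {12}, are of different kinds. They include plasma and stool concentrations (AGP, CRP, IFABP, myeloperoxidase, AAT, IGF-1, IGFBP-3), stool pH and anthropometry.

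The section Sample size {14} argues that treating biomarkers as continuous will raise power, and illustrates this on a log scale: "we predict a mean log_10_ value of − 0.24 g/L in controls based on data from Zimbabwe". The target is that "mean AGP concentration is 20% lower in the intervention compared with the control group with 90% power at the 5% significance level", for which it gives 102 infants.

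**The concern.** The planning example uses a log10 mean and a proportional effect. The analysis rule, read plainly, estimates an arithmetic difference on the measured scale. These are different quantities: an arithmetic mean difference does not directly estimate a 20% reduction.

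There is also a question of efficiency. Concentrations cannot be negative. If they are right-skewed, a few high values dominate the arithmetic mean and its standard error, and proportional reductions become harder to detect. The gain in power that Sample size {14} expects from continuous analysis would then be partly lost. The rule covers most laboratory secondary outcomes, up to four visits each.

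**Working it through.** **Inputs from the article.** Control mean log10 AGP −0.24; 20% reduction; 90% power; 5% level (taken as two-sided); 102 infants; 131 per arm and alpha 0.0167 from the primary calculation. No SD is given for any marker.

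**1. The plan's own figure.** Without an SD, 102 cannot be reproduced independently, so I solved for the SD. The difference on log10 is −log10(0.8) = 0.0969. From n per arm = 2 × SD² × (1.960 + 1.282)² / 0.0969²:

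- 102 per arm: SD = 0.0969 × √(102/2) / 3.242 = 0.2135 (0.49 on the natural log).
- 102 in the two arms together, 51 each: SD = 0.0969 × √(51/2) / 3.242 = 0.151 (0.35 on the natural log).

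The wording allows either reading, so I carry both.

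**2. AGP, log scale against untransformed.** For log-normal data with natural-log SD s and ratio R = 0.8, CV² = exp(s²) − 1, and the untransformed test has

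power ≈ Φ{ (1 − R) / √[CV² (1 + R²)/n] − 1.960 }.

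- n = 102, s = 0.492: CV² = 0.273; 0.2 / √(0.273 × 1.64/102) = 3.02; power = Φ(1.06) ≈ 0.855.
- n = 51, s = 0.348: CV² = 0.128; 0.2 / √(0.128 × 1.64/51) = 3.11; power = Φ(1.15) ≈ 0.875.

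Simulation (20,000 two-arm comparisons per row, two-sample t-test) agrees:

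| n per arm | log10 SD | log scale, 5% | untransformed, 5% | log scale, 0.0167 | untransformed, 0.0167 |
|---|---|---|---|---|---|
| 51 | 0.151 | 89% | 87% | 79% | 76% |
| 102 | 0.2135 | 90% | 86% | 80% | 74% |
| 131 | 0.2135 | 95% | 93% | 89% | 85% |

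The loss for AGP is 2 to 4 points at 5%. At 0.0167 it is about 3 points for the smaller SD and about 4 to 6 for the larger one.

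**3. More skewed markers (SDs assumed).** With 131 per arm and alpha 0.0167, the effect at each SD was set for 80% log-scale power: log10 difference = SD × (2.393 + 0.842) × √(2/131) = 0.400 × SD. Repeated simulation runs differed by 1 to 2 points.

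| assumed log10 SD | ratio used | untransformed power |
|---|---|---|
| 0.3 | 0.76 | about 67% |
| 0.4 | 0.69 | about 58% |
| 0.5 | 0.63 | about 48% |
| 0.6 | 0.58 | about 38% |

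The effect changes from row to row. The table compares the two scales at a given SD; it does not show power for a fixed 20% reduction. For that fixed effect at 131 per arm, 5% level and natural-log SD 1.0 (log10 SD 0.43), power is 44% on the log scale and 30% untransformed.

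**The case against.** The strongest reply is that the article never says the values are untransformed. A normal, identity-link model is also the usual model for log values, on which a mean difference is a log ratio. The rule is generic and covers outcomes such as stool pH, where no log is wanted, and the log10 example suggests the team expects to work on that scale. The article refers to a statistical analysis plan, not shown here, which may settle this.

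Part of that stands. The measured scale is the natural reading of a mean difference, but it is an inference. A reader might infer that the plan forbids transformation; the text does not support that. Still, the article fixes distribution, link and effect measure for all continuous outcomes, and those choices followed literally do not match its planning scale.

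The second reply also stands: the log10 figure is given only as an illustration ("Using AGP as an example"), and for that marker the loss is small. The larger losses rest on assumed SDs, on alpha 0.0167, which the article assigns to the primary comparisons and not to this example, and on effects larger than 20% (about 42% at log10 SD 0.6).

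A reader might combine the log10 mean of −0.24 with the predicted 35% of controls above 1 g/L, obtain a log10 SD of about 0.24/0.385 = 0.62 under log-normality, and conclude that AGP itself is strongly skewed. The two figures come from different cited sources, so this does not establish it.

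Finally, with about 131 per arm an arithmetic mean difference is a valid contrast. The issue is efficiency and consistency, not bias.

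**Conclusion.** The point holds in a limited form. As written, the analysis of continuous biomarkers is on a different scale from the one used to plan continuous AGP, and it is less efficient for right-skewed concentrations.

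For AGP the cost is minor at the SD implied by the article's own N. For other markers it could be substantial, with about 80% power falling to between 67% and 38%, but only if their log10 SDs are around 0.3 to 0.6. The article neither confirms nor excludes such values. All these figures assume log-normal data and a proportional effect.

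Two stronger readings are not supported: that the plan loses much of its power for AGP, and that the trial's main comparison is weakened. The primary outcome is AGP above 1 g/L, analysed as a proportion, and is untouched. Only secondary analyses, in a trial that calls itself exploratory, are affected.

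**What to change.** In {20a}, state that right-skewed plasma and stool concentrations (AGP, CRP, myeloperoxidase, AAT, IFABP), with their baseline covariates where available, are log-transformed before the generalised linear and mixed-model analyses. Report them as geometric mean ratios with 95% confidence intervals. Keep mean differences for stool pH and anthropometry, and for IGF-1 and IGFBP-3 unless blinded data show skew.

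This changes wording only and needs no new data or participants. There are two small costs: values below the detection limit need a substitution rule, and the effect becomes a ratio instead of an arithmetic difference. The ratio matches the proportional effect used in planning. The choice should be fixed before allocation is released to the study team.

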### Outcomes {12}

#### Primary outcome

The primary outcome will be raised plasma AGP concentration (> 1 g/L) at age 6 months as a key biomarker of poor gut health contributing to chronic systemic inflammation and impaired growth.

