## Statistical methods

### Statistical methods for primary and secondary outcomes {20a}

Demographic, clinical and laboratory data and also variables reflecting feeding, WASH practices and environmental factors will be summarised using simple descriptive statistics. Continuous variables will be summarised according to the number of subjects with non-missing data as mean, standard deviation, median, minimum and maximum. Categorical variables will be summarised according to the absolute frequency and percentage of subjects in each category level. The denominator for the percentages is the number of subjects with data available unless noted otherwise.

The primary outcome analysis will be based on the intention-to-treat (ITT) population which will include all randomised study subjects. The proportion of infants aged 6 months with abnormal AGP concentration (> 1 g/L) in each intervention arm will be compared with the proportion in the control arm. Data will be analysed using generalised linear models with treatment as the only predictor, AGP concentration at baseline as covariate, binomial distribution and log link function, generating the estimates of treatment effects in relative risk and their 95% confidence intervals (CI). Covariate-adjusted analysis will also be performed with covariates that affect the primary outcome (e.g. season of birth, HIV exposure, mode of delivery, mode of feeding, exposure to antibiotics, WASH and environmental factors such as water source, sanitation facilities, hygiene practices, use of soap, number of siblings, proximity to animals). Subgroup analysis will also be performed on the covariates used in the covariate-adjusted analysis.

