### Methods in analysis to handle protocol non-adherence and any statistical methods to handle missing data {20c}

Analyses of the PP population will be a sensitivity analysis to investigate whether conclusions are sensitive to assumptions regarding compliance with the dietary supplements and missing data. Maximum efforts will be made to avoid missing values; however, where this does occur, missing data will be reported and left out of analyses.

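### The per-protocol analysis is presented as the check on missing-data assumptions but cannot test them, which leaves the complete-case primary analysis without a sensitivity analysis for missing 6-month AGP

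*Protocol article*

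**What the plan says.** All of the relevant text is in the protocol article.

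- **Outcome (Primary outcome).** "The primary outcome will be raised plasma AGP concentration (> 1 g/L) at age 6 months". This is one binary result per infant, from a blood sample taken at a clinic visit.
- **Population (section {20a}).** "The primary outcome analysis will be based on the intention-to-treat (ITT) population which will include all randomised study subjects".
- **Primary model (section {20a}).** "generalised linear models with treatment as the only predictor, AGP concentration at baseline as covariate, binomial distribution and log link function". A covariate-adjusted version is also planned.
- **Missing values.** Section {20a} reads, in part, "Missing data will be treated as missing completely at random in the GLMMIX model analysis and no imputation of primary or secondary endpoints". Section {20c} adds the general rule: "missing data will be reported and left out of analyses".
- **Named check (section {20c}).** The per-protocol analysis is to show whether conclusions are "sensitive to assumptions regarding compliance with the dietary supplements and missing data".
- **Per-protocol definition (section {20a}).** Randomised infants who complete at least 75% of supervised doses. Under Intervention description {11a}, Arm 4 receives no supplement.
- **Expected loss (Sample size {14}).** 131 infants per arm are needed and 150 are recruited, to allow for 13% dropout.

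**The concern.** The population is described as everyone randomised, but an infant with no 6-month AGP cannot enter the analysis once imputation is ruled out and missing values are left out. What remains is a comparison of infants who were alive, retained and sampled at 6 months. That comparison is sound only if, given arm and the covariates in the model, having a result is unrelated to what the result would have been.

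The protocol itself describes routes by which this could fail. Mortality and hospital admission are listed outcomes. Under section {11b}, mothers may withdraw an infant from the study if they think the supplement is causing harm, and that reason can arise only in the supplemented arms of an open-label trial. None of this shows that loss will be informative, but it is reason to test the assumption.

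The test the protocol names cannot do that. If the per-protocol and primary results agreed, the trial would report that its conclusions are robust to missing data although nothing about the missing infants had been varied.

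**Working it through.** **1. The plan's own figures.** Inputs from Sample size {14}: 35% v 17.5%, alpha 0.0167, power 80%. For a two-sided test with pooled variance and no continuity correction:

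n = [z(1−α/2)·√(2·p̄·(1−p̄)) + z(0.80)·√(p1(1−p1) + p2(1−p2))]² / (p1 − p2)²

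With p̄ = 0.2625, z = 2.393 and z = 0.842, n = 130.9, so 131 per arm, as stated. The plan thus expects 150 − 131 = 19 infants per arm (19/150 = 12.7%) without a primary outcome. The sample size is not in dispute.

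**2. What the per-protocol analysis does to those infants.**

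| Requirement for a missing-data check | Per-protocol analysis as defined |
|---|---|
| Represents infants without a 6-month AGP | No: no imputation, and missing values left out |
| Varies the assumption about their outcomes | No: it varies only the adherence threshold |
| Keeps the randomised comparison | No: removes further infants after randomisation |
| Same rule in every arm | No: controls have no doses to complete |

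The criterion also selects on retention. Ten daily doses plus roughly 24 weekly doses is about 34, and 75% of that is about 26, or the ten daily doses and some 16 weekly ones. A supplemented infant lost before about 4 months cannot reach the threshold. The set therefore excludes many of the infants in question by construction.

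**3. How far missing infants could move the primary result.** Assume 131 observed and 19 missing per arm, with observed risks of 35% (control) and 17.5% (supplemented). Let m_t and m_c be the risks among the missing supplemented and control infants:

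RR = (131 × 0.175 + 19·m_t) / (131 × 0.35 + 19·m_c) = (22.925 + 19·m_t) / (45.85 + 19·m_c)

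| Missing infants' risk | m_t | m_c | Calculation | RR |
|---|---|---|---|---|
| As observed, both arms | 0.175 | 0.35 | 26.25/52.5 | 0.50 |
| Twice observed, both arms | 0.35 | 0.70 | 29.575/59.15 | 0.50 |
| Twice, supplemented only | 0.35 | 0.35 | 29.575/52.5 | 0.56 |
| Three times, supplemented only | 0.525 | 0.35 | 32.9/52.5 | 0.63 |
| All supplemented raised, no controls | 1 | 0 | 41.925/45.85 | 0.91 |
| No supplemented raised, all controls | 0 | 1 | 22.925/64.85 | 0.35 |

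**4. Would the conclusion change?** A pooled z-test on 150 per arm, treating the filled-in values as if observed (so only approximate), gives p of about 0.003 at RR 0.56 and about 0.012 at RR 0.63. Both are below 0.0167. With missing controls kept at 35%, p reaches 0.0167 when the missing supplemented risk is about 57% (57/17.5 = 3.3 times observed).

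**The case against.** The strongest reply has four parts.

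**The missing-completely-at-random statement does not cover the primary outcome.** This is correct. A reader might infer from section {20a} that the protocol assumes this mechanism for 6-month AGP. The sentence ties it to the mixed model, which the same section reserves for secondary outcomes with repeated measurements. For the primary model only the exclusion of missing values and the ban on imputation are stated. A complete-case model also tolerates missingness that depends on terms in the model, and the covariate-adjusted analysis loosens the requirement further. That analysis is not presented as a missing-data check, however, and it leaves out the same infants.

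**Bias is not shown.** This is also correct. Controls get the same home visits, laboratory staff are blinded, mothers unlikely to stay are excluded, and retention measures are listed. The 13% is a planning allowance. Equal relative increases in both arms leave the RR at 0.50, and the two moderate one-sided cases stay below 0.0167. A reader might infer that the primary result will be biased or lost, but the documents do not support that.

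**Earlier AGP may help little.** The documents give no correlation between earlier and 6-month AGP, and infants lost early may lack the 6-week and 3-month samples too. The gain from imputation is unknown. This supports using it as a sensitivity analysis and not as the primary one.

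**Such detail belongs in the analysis plan.** This holds for imputation models and tipping-point settings. It does not hold for a stated ban on imputing the primary endpoint or for a stated purpose that the per-protocol analysis cannot serve. An analysis plan that added imputation would contradict section {20a}.

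**Conclusion.** The point stands in a limited form. The protocol states a check on missing-data assumptions that cannot perform that function, and its other rules make the primary analysis of all randomised infants a complete-case analysis with no other missing-data check named.

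For a planned effect of RR 0.50 with 19 of 150 missing per arm, the RR over all randomised infants ranges from 0.50 under proportionate loss to 0.56 or 0.63 under moderate one-sided loss, with outer limits of 0.35 and 0.91. These figures assume that the planned risks are seen in the observed infants and that loss is equal across arms. They show that the expected loss is large enough to need examining, not that the result will be wrong.

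The complete-case model is a defensible primary analysis. A reader might conclude that imputation must replace it, or that deaths must be counted as raised AGP. Neither follows: a 6-month AGP does not exist for an infant who has died, counting deaths as unfavourable defines a different, composite outcome, and mortality is already a secondary outcome.

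The mixed-model wording is a lesser matter. A likelihood-based mixed model needs only missing at random, so the stated assumption is stronger than necessary.

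**What to change.** 1. Keep the complete-case generalised linear model as the primary analysis, and say plainly that it uses infants with a 6-month AGP result.
2. In section {20c}, remove missing data from the stated purpose of the per-protocol analysis, so that it addresses compliance only.
3. In section {20a}, amend the ban on imputation to allow a pre-specified sensitivity analysis of the primary outcome: multiple imputation by arm under missing at random, for surviving infants, using 6-week and 3-month AGP and CRP, HIV exposure, birth anthropometry and illness episodes.
4. Follow it with a delta-adjusted (tipping-point) analysis that varies the missing infants' risk separately in each arm, because equal relative shifts leave the RR unchanged.
5. Report deaths before 6 months by arm beside these results.
6. For the repeated-measures mixed models, replace missing completely at random with missing at random. This corrects the wording and does not change the estimates.

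The cost is a little extra analysis work on data already scheduled for collection. No visit, sample or participant is affected. The changes should be settled before the analysis plan is signed off and the allocation released, as section {17a} describes.

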### Justification for the study

The gut microbiome is critical for the development of the gut, brain and other organs, mucosal and systemic immunity and protection against gut infection through colonisation resistance [24–27]. In healthy, breastfed infants, bifidobacteria flourish and become abundant. Bifidobacteria facilitate further gut colonisation by a diverse range of anaerobes by “cross-feeding” through hydrolysis of complex carbohydrates and the production of organic acids. Some strains of lactobacilli and bifidobacteria have direct immune-modulatory, anti-inflammatory and anti-pathogen effects, the latter partly mediated through acidifying the intestinal lumen through increased production of organic acids [24, 28, 29]. As key “pioneer” organisms creating the right environment in the gut for colonisation with a broad range of healthy anaerobic bacteria, lactobacilli and bifidobacteria may have long-term benefits that persist into adult life reducing the risk of common metabolic diseases as well as improved long-term gut health and immunity [25].

Several common environmental factors may either delay or disturb the development of the gut microbiome resulting in dysbiosis. These include Caesarean section delivery, hospital admission, maternal/infant antibiotics, poor hygiene and sanitation, parasite infection and faulty feeding practices [29–34]. Additionally, maturity at birth has been found to affect microbiota development with those extremely premature infants at risk of delayed microbiota development [35]. Several studies have reported delayed maturation of the gut microbiome and a deficiency of *Bifidobacterium* in children with malnutrition [36].

Administration of pro- or synbiotics may be a feasible, safe and effective means of building the resilience of the developing gut microbiome against environmental factors in early life. Probiotics are live, non-pathogenic microorganisms that, when administered in adequate amounts, confer a health benefit on the host [37]. Commonly used probiotics are strains of lactobacilli and bifidobacteria. Prebiotics are defined as substrates that are selectively utilised by host microorganisms conferring a health benefit [38]. Prebiotics are present in breast milk as human milk oligosaccharides. Oligosaccharides are commonly used prebiotics and increase bifidobacteria and related taxa [38]. Synbiotics combine prebiotics with probiotics.

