### Participant timeline {13}

Pregnant women and families will be provided with information about the study when attending ANC during the third trimester. Following the delivery of a live infant, newborns will be assessed by study staff according to the inclusion/exclusion criteria within the first 3 days after birth. After securing informed consent, newborns will be allocated randomly to one of the 4 study arms. Study staff will undertake a Ballard assessment to determine gestation, measure anthropometric indices and record infant feeding, WASH practices and environmental information using standardised questionnaires. Study staff will confirm that the infant has taken at least one breastfeed well and then assist the mother/carer in administering the first dose of the appropriate dietary supplement in infants allocated to the active study arms.

Study staff will visit daily for the following 9 days and then weekly to age 6 months to supervise the administration of the pro/synbiotic to infants in the intervention arms. The same visit schedule will be applied to infants in the control arm (no dietary supplement). At all visits, research staff will encourage exclusive breastfeeding and other positive health practices and facilitate transport to the clinic as required in unwell infants. Follow-up visits for all participants to collect data and stool and blood samples will be scheduled for 6 weeks, 3 months, 6 months and 12 months. A final follow-up visit at 2 years will be scheduled to record long-term outcomes (Fig. 1).

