## Assignment of interventions: allocation

### Sequence generation {16a}

The trial statistician at LSTM, UK, will prepare computer-generated random allocation sequences using blocks of random size and stratified according to HIV exposure. The allocation ratio will be 1:1:1:1.

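### Gestation is measured in a cohort that admits preterm infants, but the stated growth model leaves it out; adding it is a nearly free gain in precision, not the correction of a bias

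*Protocol article*

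**What the plan says.** All of this comes from the protocol article.

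- **Who enters.** Eligibility criteria {10} require a weight of at least 2000 g. Neither the inclusion nor the exclusion list sets a gestational-age limit, so preterm infants above that weight are eligible.
- **Gestation is known.** Participant timeline {13}: "Study staff will undertake a Ballard assessment to determine gestation". Justification for the study gives a reason to care about it: "maturity at birth has been found to affect microbiota development".
- **Growth outcomes.** Statistical methods {20a} derive z-scores from the WHO 2006 standards ("scores will be calculated using the WHO Anthro Survey Analyser and WHO 2006 child growth standards") and plan both comparisons at time points and "growth expressed as change in indices over time". Gain in weight, length and head size to age 2 years is a secondary objective.
- **Growth model.** The same section lists arm, visit and arm-by-visit as fixed effects, with "baseline measurement of an outcome as covariate, and subject as random effect". Gestation is not among the terms.
- **Other adjustment.** "Covariate-adjusted analysis will also be performed with covariates that affect the primary outcome (e.g. season of birth, HIV exposure" opens a list that does not name gestation. It is a list of examples, and it concerns the primary outcome, not growth.
- **Allocation.** Sequence generation {16a}: "The allocation ratio will be 1:1:1:1", stratified by HIV exposure only.

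**The concern.** An infant born early is less far along the growth curve than a term infant of the same age since birth. If both are scored at chronological age, the preterm infant gets a low z-score for being early, not for growing badly. The deficit is large in the first weeks, when growth is fast and the reference SD is small, and nearly gone by 2 years. The z-score therefore rises without any real catch-up.

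In a trial about growth faltering, this affects the early z-score levels and the within-arm change. It also leaves variation in the growth outcomes that a variable already on the case report form could explain. The single baseline term deals with it only in part, because the gestation effect shrinks with age while the article specifies no baseline-by-visit term.

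**Working it through.** **1. The plan's own figure.** The only sample size stated is for raised AGP: 35% against 17.5%, 80% power, α = 0.0167. With the pooled-variance formula, two-sided, without continuity correction:

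n = [2.393·√(2·0.2625·0.7375) + 0.842·√(0.35·0.65 + 0.175·0.825)]² / 0.175² ≈ 131 per arm, or 524 in total.

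This matches the article. No sample size or power is given for growth, so nothing stated there changes.

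**2. One preterm infant (assumed growth rates).** The z error per week of prematurity is weekly length gain divided by reference SD.
- At 6 weeks: 0.8/2.1 to 1.0/1.9, about 0.4 to 0.5 z per week. An infant born at 35 weeks (5 weeks early) scores 1.9 to 2.6 z too low.
- At 2 years: 0.23/3.1 = 0.07 z per week, so about 0.4 z too low.

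**3. An arm mean.** With an assumed preterm share of 5% to 20% and a shift of 0.5 to 2.0 z per preterm infant, the mean moves by share × shift: 0.05·0.5 = 0.03 up to 0.20·2.0 = 0.40 z too low. The apparent within-arm rise is share × (early shift − later shift):
- 10% preterm, 1.5 falling to 0.5 z: 0.10·1.0 = 0.10 z.
- 20% preterm, 2.0 falling to 0.5 z: 0.20·1.5 = 0.30 z.

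**4. Between arms.** The same two scenarios were simulated: 4,000 runs, 131 per arm, SD 1.2 (the local survey SD in Study setting {9}), baseline-to-follow-up correlation 0.5 assumed.
- No true effect: the arm difference in change was −0.003. Type I error was 5.2% to 5.4% for change scores and 4.7% to 5.4% for baseline-adjusted analysis.
- True effect 0.25 z: recovered as 0.25 by both analyses.

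**5. Precision without baseline adjustment.** SD = √(1.2² + p(1−p)·shift²).

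| Preterm share | Shift (z) | SD | Power for 0.25 z at 131 per arm |
|---|---|---|---|
| none | – | 1.20 | 39% |
| 5% | 0.5 | 1.21 | 39% |
| 10% | 1.5 | 1.28 | 35% |
| 20% | 2.0 | 1.44 | 29% |

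**6. Precision with the planned baseline covariate.** In the two-visit simulation of step 4, power without and with a preterm term was 48.8% and 48.8% (10% preterm), and 48.4% and 49.8% (20% preterm).

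That setting has one follow-up visit, so its baseline slope fits that visit. Over several visits a common slope fits less well. With 12% preterm, a lag of 0.5 z per week at birth falling to 0.07 at 2 years, and baseline correlation falling from 0.8 to 0.45 (all assumed), one slope left preterm infants about 0.8 z below term infants at 6 weeks and about 1.0 z above them at 2 years.

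Reduction in residual variance from adding gestation by visit, with 8% to 18% preterm assumed:

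| Baseline slope | 6 weeks | 3 and 6 months | 24 months |
|---|---|---|---|
| One slope for all visits | 6% to 10% | 0% to 1% | 5% to 8% |

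With a slope that varies by visit, the reduction was only about 0.3% to 2.4%. A separate simulation holding birth z, with Ballard error SD 1.5 weeks, gave 3% to 4% at 6 weeks, 2% to 3.5% at 3 months and under 1% from 6 months. Together these give about 0% to 4%.

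**7. Would corrected-age z-scores do better as the main measure?** Corrected age is chronological age − (40 − gestation in weeks).
- At enrolment an infant born at 35 weeks has a corrected age of about −5 weeks, so there is no usable baseline z.
- At 6 weeks the corrected age is non-negative only if 6 − (40 − gestation) ≥ 0, that is, from 34 weeks' gestation.
- Correcting only below 37 weeks creates a step of 3 weeks × 0.4 to 0.5 = 1.2 to 1.5 z at 6 weeks, placed by a measure with its own error.

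**The case against.** The strongest reply is that the article never says chronological age will be used. It names a tool and a reference, and the age convention is the kind of detail a condensed article leaves to the full protocol or SAP, which are not shown. That stands: a reader might infer that preterm infants will be scored wrongly, but this holds only if no correction is made.

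Second, a reader might infer that the growth comparisons are biased. They are not. Step 4 shows no shift and no inflation of type I error. Chance imbalance in preterm share (SD √(2·0.12·0.88/131) = 4.0 percentage points at 12% preterm) is ordinary sampling variation and already sits in the standard error.

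Third, it is tempting to set the within-arm rise of 0.10 to 0.30 z beside the effects of 0.25 and 0.16 that the Background cites. Those are differences between arms at about 2 years. The artefact is a change within every arm, so the two are not comparable.

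It is also fair that gains in centimetres or kilograms carry no z-score reference artefact, that every preterm share and growth rate above is assumed, and that the covariate list is open. None of this removes the narrower point. The article does list the terms of its growth model, and a measured baseline variable that predicts early growth is not among them.

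**Conclusion.** The point holds as a minor improvement. Preterm infants can enter, gestation is recorded, and the stated growth model does not use it. If chronological age is used, early z-score levels and within-arm change will mix prematurity with growth faltering and should not be read as faltering or catch-up alone. Treatment comparisons remain valid.

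The avoidable loss is about 0% to 10% of residual variance by visit under a single baseline slope, largest at 6 weeks and 24 months, and about 0% to 4% if the slope varies by visit. Much of the larger figure therefore comes from forcing one slope across visits. These sizes rest on an assumed preterm share of 8% to 18%, assumed growth lags and an assumed baseline correlation; the article gives none of them. The documents do not support calling the growth analysis invalid, nor making age-corrected z-scores the main measure.

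**What to change.** Add Ballard gestation at birth, as a continuous baseline covariate with a visit interaction, to all anthropometric models, including the change-in-index analysis. State in the SAP which age enters the main z-scores. Report z-scores at gestation-corrected age as a sensitivity analysis only, at visits where corrected age is not negative. Do not switch the main z-scores for infants below a 37-week cut-off.

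The cost is a sentence or two in the SAP and a few lines of code. No new data are needed, and the primary outcome and the totals of 524 and 600 are unaffected. The small downside is that error in the Ballard estimate (1 to 2 weeks assumed) limits the gain.
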